### Data analysis and outcomes

Subjects will be included chronologically and successively as soon as they meet the inclusion criteria and have given their consent to participate. The monocentric nature of the study, the small number of subjects and the expertise of the UEN staff involved in the study will limit the number of missing data. Data will be collected using observation notebooks specific to the study, using the Skezia software with secure access (https://skezia.io/). The software allows quality control of the data and monitoring of modifications, with the date and name of the person who made the modifications.

Our primary outcome is the isolation and culture of at least one isolate of each species of interest, previously identified by metagenomic data analysis and literature review (Table 1). The metagenomic identification of additional bacterial species of interest will rely on the bioinformatical and biostatistical of the French Milieu Intérieur cohort [47] for which we have obtained the consortium's agreement for use within the strict framework of this project (see iTARGET in https://www.milieuinterieur.fr/en/about-us/collaborations/), and additional public shotgun metagenomic datasets [10].

The secondary outcomes will be to first obtain metagenomic profiles of the faecal microbiota using a high throughput shotgun sequencing strategy [48] in order to identify the participant carriers for bacteria of interest in relation to their dietary profiles [10,49,50]. Combined analysis of metagenomic data, health records and diet profiles will be performed under the R software (version 3.6) [51]. Second, we aim to acquire phenotypic and genetic and/or genomic characteristics of the isolates, including growth parameters, production of bacterial metabolites, general sugar metabolisms, 16S rDNA sequencing and functional potential through genome annotation. We will collect and characterize at least one strain per donor and per media for the selected species of interest (Table 1).

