## Abstract

Recent advances in the study of the gut microbiota has pointed to its under-utilized source of potentially beneficial bacteria, known as next generation probiotics, offering a promising avenue to restore or compensate impaired gut microbiota toward a healthy state. Aside from the difficulties to achieve in-lab adequate culture conditions, the use of beneficial bacterial isolates is also limited by their bioavailability in the donor itself. In the iTARGET study, we positively selected donors based on their diet enriched in fiber, that has been shown to increase the prevalence of bacterial species associated with health.

The iTARGET study is a monocenter, prospective, observational study of adults with healthy lifestyle and high daily fiber consumption. We aim to recruit individuals in two phases, the first one for all individuals that will permit the identification of carriers for bacteria of interest and the second phase for a subset of individuals to allow for culture and isolation of previously identified potentially beneficial bacteria. Our primary outcome is the isolation and culture of at least one potentially beneficial isolate. The secondary outcomes comprised the high throughput metagenomic profiles of the intestinal microbiota and the characterization of the cultured isolates.

The study was approved by the French Research Ethics Committees (Comité de Protection des Personnes Sud-Est I) under the National reference ID 2023-A01677–38. Study findings and results will be published in peer-reviewed Open Access journals. (Trial registration number on ClinicalTrials.gov: NCT06166810).

Specifications table

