### Description of protocol

**Study aims**

The primary aim of the study is to isolate bacteria from stools of participants on a high-fiber diet, comprising new isolates of known species (list of selected species in Table 1) or new species for which no isolates have yet been cultured (Fig. 1). The secondary objectives of the study are (i) to characterize the microbiota of the recruited participants in order to identify carriers for bacteria of interest in relation to their diet, and (ii) to characterize isolated bacteria at the phenotypic and genotypic levels.

**Table 1 tbl0001:** Selected bacteria of interest for their isolation and culture in the iTARGET study [20].

Bacterial strain (GTDB taxonomy)	NCBI accession number	Interest	References
*Akkermansia muciniphila* DSM 22,959	GCF_000020225.1	Metabolic syndrome	[21,22]
*Bifidobacterium adolescentis* DSM 20083T	GCF_000010425.1	Intestinal barrier	[23]
*Bifidobacterium bifidum* NCTC 13,001	GCF_900,637,095.1	Colitis	[24]
*Bifidobacterium longum* spp.	GCF_000020425.1 and GCF_900,637,335.1	Gut-brain axis	[25]
*Phocaeicola vulgatus* ATCC 8482	GCF_000012825.1	Diet induced hepatic steatosis	[26]
*Bacteroides intestinalis* DSM 17,393	GCF_000172175.1	Primary polysaccharides degrader	[27]
*Bacteroides fragilis* NCTC 9343 (EN-2)	GCF_000025985.1	Primary polysaccharides degrader	[28]
*Bacteroides thetaiotaomicron* DSM 2079T	GCF_000011065.1	Primary polysaccharides degrader	[28]
*Bacteroides xylanisolvens DSM 18836T*	GCF_000273315.1	Pasteurized milk product fermented with B.xylanisolvens approved as novel food	[29]
*Bacteroides uniformis* ATCC8492	GCA_000154205.1	Post-antibiotic recovery	[30]
*Anaerostipes hadrus* BPB5	GCF_001998765.1	Butyrate producer	[31]
*Anaerostipes caccae* DSM 14,662	GCF_000154305.1	Food allergy	[32]
*Coprococcus eutactus* ATCC 27,759	GCF_000154425.1	Colitis	[33]
*Coprococcus catus* AF45–17	GCF_003433855.1	Short Chain fatty acid producer	[34]
*Coprococcus comes* ATCC 27,758	GCF_000155875.1	Chronic musculoskeletal pain(fibromyalgia)	[35]
*Roseburia intestinalis* DSM 14,610 (L1–82)	GCF_000156535.1	Polysaccharides degraders	[36]
*Roseburia inulinivorans* 2789STDY5608835	GCF_001406675.1	Metabolic syndrome	[36]
*Butyrivibrio crossotus* DSM 2876	GCF_000156015.1	Healthy diet positive association	[37]
*Ruminococcus bromii* L2–36	GCF_002834165.1	Food allergy	[38]

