### Sample size

To determine the minimum number of individuals required to achieve the project's objectives, and to provide an initial justification for our positive selection approach based on fiber consumption, we used healthy individuals from a published French cohort [46], representative of the French population we will target in the iTARGET study. The minimum number of individuals required to guarantee the detection of a species at least once was calculated for the19 selected species of interest (Table 1) using a binomial distribution with a probability of ≥ 0.95. Using this methodology, it was calculated that 4.4 ± 6.3 individuals were required to detect one of the 19 bacterial species of interest in the high-fiber diet group at least one time, while it would require 12,8 ± 34,1 individuals in the low-fiber group. Taking into account the mean and standard deviation, a minimum of 10 individuals on a high-fiber diet is required to maximize the prevalence of each of the selected microbial species of interest (Table 1).

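### The primary outcome is defined in two incompatible ways: one beneficial isolate in total (Abstract), or one isolate of each of the 19 Table 1 species (Data analysis and outcomes)

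*Protocol article*

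**What the plan says.** The article introduces its primary outcome twice, with the same opening words and different content.

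- **Abstract:** "Our primary outcome is the isolation and culture of at least one potentially beneficial isolate". The unit is the study as a whole, the threshold is one isolate, and Table 1 is not mentioned.
- **Data analysis and outcomes:** "Our primary outcome is the isolation and culture of at least one isolate of each species of interest". The sentence goes on to identify these species as the ones in Table 1. The unit is the species, and the threshold is one isolate for every species listed.

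Table 1 has 19 rows, and the Sample size section also works with 19 species. The Study aims section sets no number and describes the isolates sought as "comprising new isolates of known species (list of selected species in Table 1) or new species for which no isolates have yet been cultured". After the primary outcome, the Data analysis and outcomes section turns to further species: "The metagenomic identification of additional bacterial species of interest will rely on" other cohort data and public datasets.

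**The concern.** The primary outcome fixes what the study will be able to say it achieved. Here the two statements differ in unit, in threshold and in which isolates count. A result that isolates some but not all of the listed species, which is a very plausible result for a culture study, can be reported as meeting or as missing the primary outcome, depending on which sentence the author cites. Because both sentences stand in the current text, the choice can be made after the results are known.

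The aim adds a smaller mismatch. It admits isolates of species never cultured before, and an outcome confined to Table 1 gives no credit for them.

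**Working it through.** **1. Side-by-side classification.** Let k be the number of the 19 Table 1 species with at least one isolate. I take an isolate of a Table 1 species to be potentially beneficial, since that is why the species were listed.

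| Result | Abstract | Data analysis and outcomes |
|---|---|---|
| k = 0, no other beneficial isolate | not met | not met |
| k = 0, a beneficial isolate outside Table 1 | met | not met |
| k = 1 to 18 | met | not met |
| k = 19 | met | met |

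The two definitions agree only when nothing beneficial is isolated or when all 19 species are. No probability assumption enters.

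**2. Does the sample size settle which definition is meant?** The plan reports that "4.4 ± 6.3 individuals were required to detect one of the 19 bacterial species of interest in the high-fiber diet group" and concludes that "a minimum of 10 individuals on a high-fiber diet is required to maximize the prevalence of each of the selected microbial species of interest".

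- The mean plus one standard deviation is 4.4 + 6.3 = 10.7, close to the stated 10 (rounding up would give 11). The 4.4 ± 6.3 cannot be rebuilt, because the species prevalences are not given.
- The rule behind it is the smallest n with 1 − (1 − p)^n ≥ 0.95, where p is the prevalence of a species. At n = 10 this requires p ≥ 1 − 0.05^(1/10) = 0.259.
- The calculation is made species by species, so it leans towards the per-species definition. It concerns metagenomic detection at the first collection, not isolation and culture, and it does not address all 19 jointly. Even with detection at exactly 0.95 for each species, joint detection under independence would be 0.95^19 = 0.377.

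The sample size therefore does not resolve the conflict.

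**3. Illustration of the distance between the definitions.** The documents give no isolation probability. Assume a common per-species probability q and independence across species. Then P(at least one of 19) = 1 − (1 − q)^19 and P(all 19) = q^19.

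| q (assumed) | At least one of 19 | All 19 |
|---|---|---|
| 0.02 | 0.32 | about 0 |
| 0.10 | 0.865 | about 1e-19 |
| 0.50 | above 0.9999 | about 2e-6 |
| 0.90 | about 1 | 0.135 |
| 0.95 | about 1 | 0.377 |
| 0.99 | about 1 | 0.826 |

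For a 95% chance of success, at least one of 19 needs q = 1 − 0.05^(1/19) = 0.146, and all 19 needs q = 0.95^(1/19) = 0.9973. The middle column understates the chance under the Abstract, whose isolate need not belong to the 19.

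**4. Aim against outcome.** The aim includes "or new species for which no isolates have yet been cultured". The Abstract's wording could accommodate such an isolate. The Data analysis and outcomes wording, tied to Table 1, does not.

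**The case against.** The strongest reply is that the body of the article works per species throughout and that the Abstract is a loose condensation of it. The study is single-centre and observational, with three donors recalled for culture. The article shows no hypothesis test and no decision that turns on success or failure. Correcting one sentence might then be enough. This has force as to scale, and it makes the per-species reading the more likely intention. It does not remove the contradiction: the Abstract makes a complete statement with its own threshold, and one in total is not a shortening of one of each.

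A reader might infer more than the text supports in four places.

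- **That the species list is open-ended.** The outcome sentence is tied to Table 1, and the Sample size section counts 19. The following sentence mentions additional species but does not say that they join the primary outcome. The denominator is essentially fixed.
- **That half of the primary aim has no primary outcome.** The aim joins the two kinds of isolate with an or, and the Abstract's wording can cover a never-cultured species. Only the later wording leaves it out.
- **That Table 1 holds only named reference strains.** The *Bifidobacterium longum* entry carries two accession numbers and no strain name.
- **That one definition cannot fail.** At q = 0.10 the chance of at least one of 19 is 0.865, and at q = 0.02 about 0.32. The Background stresses how hard these bacteria are to isolate, so low values cannot be dismissed. A common q and independence are also doubtful, because the recalled donors are chosen partly for carrying the species of interest.

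**Conclusion.** The contradiction is real. Two current statements of the primary outcome classify every result with 1 to 18 of the 19 species isolated in opposite ways, and nothing in the article says which prevails. It is a conflict between two stated criteria, so it cannot be put down to detail left to a fuller document. This conclusion rests on the wording alone.

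The probabilities show only that the two criteria differ greatly in difficulty over most of the assumed range. They depend on an assumed common q and on independence, and they are not forecasts of this study's result. The gap between the primary aim and the Data analysis and outcomes wording on never-cultured species is a genuine but lesser inconsistency.

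**What to change.** Use one definition of the primary outcome in the Abstract, Study aims, and Data analysis and outcomes. One workable form is the number k of the 19 Table 1 species with at least one confirmed isolate, reported as k/19 and species by species. The count alone sets no criterion, so also state in advance which value of k meets the primary aim.

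Report isolates of never-cultured or additional species as a separately named count, and say explicitly whether they contribute to the primary outcome. This matters because the aim currently includes never-cultured species, and leaving them out of the primary outcome without comment would narrow that aim. It also matters because an isolate outside Table 1 scores nothing in k/19 although it satisfies the Abstract.

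The cost is wording only: no added participants, samples or culture work. The small downside for the authors is that a partial result is reported as k/19 and not as an unqualified success. The registry entry was not available for this review and should be checked for agreement with the chosen definition.

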## Data Availability

No data was used for the research described in the article.
